### Measurements

For the description of the sample, information on parent’s age, gender, marital status, child’s primary caregiver, education, employment, household income, and place of residence as well as child’s age, gender, diagnosis, level of care, and number of siblings are used.

Primary outcome measurements relate to *family quality of life*. For this purpose, validated questionnaires are used, which include the following dimensions:

Parents’ mental and physical health (GHQ-28) [20]Well-being (WHO-5) [21]Stress experience (PSS-4) [22]Family burden due to illness of the child (FaBel-20) [23]Family cohesion (RSA) [24]Resilience (BRS) [25]Individual stressor exposure (MIMIS, LEC) [26, 27]

Secondary outcomes of the quantitative survey are:

*Resilience factors and associated measures*
Optimism / positive thinking (SOP-2) [28]Locus of control (IE-4) [29]Self-efficacy (ASKU-3) [30]Social support (OSSS-3) [31]*access to care*
Satisfaction with health care [15]Satisfaction with health care coordination (from t1) [32]Knowledge and use of support services [33]

To assess possible over-, under- and misuse of health services the results of the process evaluation will be used. For this purpose, all FGPs involved are questioned by means of guideline-based qualitative interviews.

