## Materials and methods

### Design

A non-randomized controlled study (quantitative online survey) over 18 months is ongoing with four measurement points: baseline at the start of the intervention (t0), interim assessments after 6 (t1) and 12 (t2) months, and a final survey after 18 months (t3). In order to be able to identify at least medium effects (Cohen’s d = 0.5) [17] with a test power of 0.80 and an alpha error of 0.05, at least 52 families both from the intervention and control group are required to participate in the study. Since there are hardly any longitudinal intervention studies with particular regional differences in the field of self-help research, the extent of the regional variance (hierarchical data structure) can only be estimated. Assuming 5% intracluster variance explained by the hierarchical data structure, this sample size must be increased by the variance inflation factor [18], resulting in a minimum of 73 families per group. With an estimated drop-out rate of 20–40% based on current studies (e.g. Recapture Life-AYA study [19]), the number of samples ultimately increases to a total of N = 204 families.

The study is conducted with parents and other guardians (all genders and ethnicities) with at least one disabled and/or chronically ill child under 18 years (benefit receipt according to § 37 of Germany’s Social Security Code V and/or level of care > 1), and is limited to the main adult caregivers of the child. The families from the intervention group are recruited via the care service ‘nestwärme gGmbH’ and its network partners in three metropolitan areas of Germany (Trier, Saarbrucken and Munich). The families for the control group are recruited via the umbrella organization ‘Kindernetzwerk e.V.’, which also has regional associations in these regions. In contrast to the control group, which is supported by standard care, the intervention group receives an FGP that carries out a structured assessment in the family and accompanies the family throughout the intervention period. Recruitment for the baseline data collection already started in the intervention areas in January 2022. Control group participants were recruited throughout Germany, with 102 families consenting to take part in the study until the end of September 2022.

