### Statistical analysis

SPSS™ 27 and the programming language R are used as software for the statistical analyzes. In the first step at baseline, the data analysis is primarily descriptive according to sample characteristics and outcome measures. Subgroup analyzes between intervention and control group are made using Chi^2^ test, t-test and Mann-Whitney U test, based on the measurement/scales of the related variables. Multilevel regression models will be used to analyze the longitudinal data. This makes it possible to statistically model and control regional differences. Interaction effects are calculated to analyze group differences (intervention vs. control).

If the proportion of missing values (e.g. "don’t know", no answer) is lower than 5%, these will be excluded from the analysis in accordance with the GESIS guidelines [34]. Else, for larger proportions missing data will be imputed using the multivariate imputation by chained equations method [35].

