There are, however, a number of limitations. A possible limitation of this study is that we only use self-reported outcomes for the impact analysis of FGPs as our primary research goal. Outcomes reported by someone else (e.g. clinical data) are not planned. However, for the most part we use psychometrically tested instruments developed for different contexts and languages (incl. German). Compared to other studies using the measurements, we expect a slightly higher proportion of missing values in some items after 18 months, but tackling this issue with imputation techniques is feasible. Missing values in psychometric testing are not a problem per se, but may result in biased reliability scores [37]. Finally, the number of cases in this project is limited overall because the number of affected families and/or qualified professionals is comparatively small; not every affected family needs an FGP per se, and the offer is not sufficiently known.

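### The groups are not randomised and come through different recruitment channels, yet the article gives the collected background variables a descriptive role and names region as the only factor the longitudinal model controls

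*Protocol article*

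**What the plan says.** All places are in the protocol article.

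- **Design, allocation.** "A non-randomized controlled study (quantitative online survey) over 18 months is ongoing with four measurement points".
- **Design, recruitment.** "The families from the intervention group are recruited via the care service" nestwärme and its network partners in Trier, Saarbrucken and Munich. "The families for the control group are recruited via the umbrella organization" Kindernetzwerk, which also has regional associations in those areas. Nevertheless, "Control group participants were recruited throughout Germany".
- **Measurements.** The background variables open with "For the description of the sample, information on". The list covers the parent's age, gender, marital status, education, employment, income and residence, and the child's age, diagnosis, level of care and number of siblings.
- **Statistical analysis.** For baseline, "Subgroup analyzes between intervention and control group are made using" chi-squared, t and Mann-Whitney tests. Multilevel regression follows for the longitudinal data; the stated advantage is that regional differences can be modelled and controlled. Then: "Interaction effects are calculated to analyze group differences (intervention vs. control"). The factor that group interacts with is not named. No covariate adjustment, matching or weighting is mentioned.
- **Discussion, limitations.** Self-reported outcomes, missing values and small case numbers are listed. Selection and confounding are not.

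**The concern.** Without randomisation, the answer depends on how the analysis deals with differences between the families in the two channels. Families reached through a care service may differ from members of a self-help umbrella organisation in the child's diagnosis and age, level of care, resources, or the moment at which they sought help. Each of these may affect how quality of life and burden change over 18 months.

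The article collects most of the relevant variables but assigns them to description. Followed as written, the analysis would attribute any difference in trajectory that comes from the mix of families to the FGP. Baseline significance tests do not remedy this: they detect imbalance, with limited power, but do not adjust for it. Region cannot stand in for the other variables, because it is itself tied to group (three areas against the whole country).

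**Working it through.** The article gives no figure for confounding, so there is none to reproduce. The check has two parts.

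**1. What the named model does and does not remove**

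Assume that the interaction is group by time.

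- *Stable level differences.* If one group is always g SD worse, the gap is g at t0 and g at t3. The contrast in change is g − g = 0, so these are handled.
- *Time-constant covariates entered as main effects.* They shift a family's level equally at all four time points, so they largely cancel from the contrast. Adding them in this form would change little.
- *Covariates that affect change* (for example diagnosis, child age or income). If their distribution differs between the groups, the difference in slope goes into the group-by-time term. Neither region nor the baseline tests remove it.
- *High need at entry.* If part of the t0 gap is temporary, it shrinks without any intervention, and the shrinkage goes into the same term.

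**2. Illustration of the last item**

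Inputs from the Design section: planned effect d = 0.5; 73 families per group after the clustering allowance and 102 recruited per group (73/102 = 0.716, a dropout of about 28%, inside the stated 20–40%).

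Assumed inputs, not in the documents: t0 gap g = 0.3 to 0.5 SD; 18-month correlation r = 0.5 to 0.7.

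If both groups regress towards a common mean, the gap at 18 months is r × g, so the spurious contrast is g − r × g = g × (1 − r).

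| g | r | g × (1 − r) | share of d = 0.5 |
|---|---|---|---|
| any, stable | any | 0 | 0% |
| 0.3 | 0.7 | 0.09 | 18% |
| 0.3 | 0.5 | 0.15 | 30% |
| 0.5 | 0.7 | 0.15 | 30% |
| 0.5 | 0.5 | 0.25 | 50% |

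Effect on a nominal two-sided 5% test of change scores, with 73 per group, no true effect and clustering ignored:

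- Standard error = √(2(1 − r)) × √(2/73), where √(2/73) = 0.1655.
- g = 0.3, r = 0.7: 0.09 / (0.775 × 0.1655) = 0.70 standard errors, error rate about 11%.
- g = 0.5, r = 0.5: 0.25 / (1.0 × 0.1655) = 1.51 standard errors, error rate about 33%.

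The range is not a bound. A wholly temporary gap would regress almost completely, and a gap in the other direction would hide a benefit instead of creating one.

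**The case against.** The strongest reply is that a condensed article need not list model covariates. Saying that variables describe the sample does not exclude them from the model, and the sentence about region explains why a multilevel model was chosen. This stands in part: that no other covariate will be used is an inference, and a full protocol or analysis plan might say otherwise. However, the article is not silent. It gives the variables a role, names one controlled factor, and omits selection from its limitations, in a design where confounding control is central to the comparison.

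Three further points stand:

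- Eligibility criteria are stated for the study as a whole (child under 18, benefit receipt under § 37 and/or level of care above 1, main adult caregiver). Together with a group-by-time contrast, this limits differences in level. What remains is differential change.
- A reader might infer from "not every affected family needs an FGP per se" that need decided who entered the intervention group. The Discussion offers that remark to explain small case numbers. It says nothing about allocation, so need-driven entry remains a possibility, not a documented fact.
- A reader might take 18–50% of the planned effect as an estimate of bias in this trial. It is not: both inputs are assumed, the direction of the gap is unknown, and the bias is zero if the gap is stable.

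**Conclusion.** The concern holds in limited form. As the article is written, differences in change that arise from who entered through each channel are not controlled, although most of the variables needed to reduce them are collected. The size is unknown: the illustration runs from 0 to 0.25 SD and rests on an assumed gap, an assumed correlation and a group-by-time reading of the interaction.

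The documents do not support the stronger statements that the plan rules out covariate adjustment, that the groups are known to differ in need, or that a particular share of any observed effect would be spurious.

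**What to change.** - **Primary analysis.** Make the longitudinal comparison confounder-adjusted and name the second factor of the interaction. Use a short, pre-specified set of t0 variables already collected, for example child age, diagnosis group, level of care, siblings, and parental education, employment, income and marital status. Enter them with time interactions or through propensity-score overlap weights, not as main effects alone.
- **t0 outcome score.** Add it to the weighting model, or run an ANCOVA-type analysis. Background variables alone remove regression to the mean only as far as they predict the temporary part of the score. ANCOVA has its own assumption: if the gap is in fact stable, it errs by the same g × (1 − r) in the opposite direction. It should therefore be reported beside the change-based result.
- **Balance.** Report standardised mean differences and overlap before and after adjustment, instead of relying on baseline significance tests.
- **Reporting.** Keep the unadjusted model as a sensitivity analysis, and state residual confounding by recruitment channel as a limitation.

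**Cost.** No new data, and modest analyst time. Adjustment loses some effective sample size and precision, which matters with 73 to 102 families per group, so the covariate set should stay small. Place of residence is closely tied to group and should enter only if overlap allows. With overlap weights, the result applies to families who could plausibly have come through either channel. Controls were enrolled until the end of September 2022, so their 18-month data run to about March 2024. This is after the article's publication in July 2023, so at that point the change could still be fixed before the final data.

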**Methods:**

We are carrying out a non-randomized controlled trial with four points of measurement (t0-t3 in 18 months), beginning in January 2022. Both intervention and control group include 102 families. Primary outcome measure is the quality of life, secondary outcomes are resilience factors and associated measures as well as the access to care. Multilevel regression models will be used to analyze the longitudinal data.

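### The single primary outcome is listed as eight instruments at three follow-ups with no deciding test, while alpha 0.05, power 0.80 and the sample size assume one comparison

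*Protocol article*

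**What the plan says.** The Methods paragraph of the abstract treats the primary outcome as one thing: "Primary outcome measure is the quality of life, secondary outcomes are resilience factors and associated measures as well as the access to care".

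Under Measurements, the primary outcome is family quality of life, for which "validated questionnaires are used, which include the following dimensions". Seven dimensions follow, measured with GHQ-28, WHO-5, PSS-4, FaBel-20, RSA, BRS and, for the last dimension, both MIMIS and LEC. That makes eight instruments. The last entry reads "Individual stressor exposure (MIMIS, LEC").

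Under Design, the schedule after baseline is "interim assessments after 6 (t1) and 12 (t2) months, and a final survey after 18 months (t3"). No wave is called primary. The same section sizes the trial "In order to be able to identify at least medium effects" (d = 0.5) "with a test power of 0.80 and an alpha error of 0.05". This gives 52 families per group, 73 after a variance inflation factor and 204 in total after dropout. The calculation is not tied to an instrument or a time point, and its sidedness is not given.

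Under Statistical analysis, the longitudinal data go into multilevel regression models, with interaction effects for the group comparison. No outcome, composite, testing order or contrast is singled out.

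**The concern.** A sample size at one alpha and one power presupposes one test that decides the question. Here the primary outcome is a list of eight instruments, and the article does not say how a mixed result would be read. The claim could be settled after the scales have been seen. This matters more than usual because the trial is not randomized, all impact outcomes are self-reported, and the Discussion expects the results to be applied in standard care.

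The list also contains an entry of a different kind. Individual stressor exposure is, by its own label, a measure of what the respondent is exposed to. As listed, a group difference on MIMIS or LEC alone would be a result on the primary outcome, quality of life.

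**Working it through.** **Inputs from the article.** d = 0.5, power 0.80, alpha 0.05, 52 then 73 per group, N = 204 (Design); eight instruments (Measurements); three follow-ups (Design). Correlations between scales are not given. I assume 0.3, 0.5 and 0.7, equal for all pairs.

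**1. The plan's own figure.** For two means with SD 1, n per group = 2(z_alpha + z_beta)²/d².
- One-sided 5%: 2(1.645 + 0.842)²/0.25 = 49.5, so 50 (t test: 51). This is within 2 of the stated 52.
- Two-sided 5%: 2(1.960 + 0.842)²/0.25 = 62.8, so 63 (t test: 64). This does not reproduce 52.
- Power of one t test at 52 per group: 0.81 one-sided, 0.71 two-sided.
- Inflation: 73/52 = 1.404, so 73 evaluable families per group correspond to an effective 52.

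The stated size is therefore a one-test size, and it fits a one-sided alpha.

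**2. Any scale counts as success.** With k = 8 tests at two-sided 5%:
- Independent: 1 − 0.95⁸ = 0.337.
- Equal correlation ρ: 1 − ∫[Φ((c − √ρ·u)/√(1−ρ)) − Φ((−c − √ρ·u)/√(1−ρ))]⁸ φ(u) du, with c = 1.960.
- Favourable direction only: the same integral without the second Φ term. Independent: 1 − 0.975⁸ = 0.183.

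| Correlation | Either direction (nominal 5%) | Favourable only (nominal 2.5%) |
|---|---|---|
| 0 | 34% | 18% |
| 0.3 | 30% | 15% |
| 0.5 | 25% | 13% |
| 0.7 | 19% | 10% |

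At one-sided 5%, the level that fits 52, c = 1.645 in the favourable-only integral gives 27%, 22% and 17% at ρ = 0.3, 0.5 and 0.7.

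**3. Each wave tested separately as well.** This gives 8 × 3 = 24 tests. Independent, two-sided: 1 − 0.95²⁴ = 0.71. With all 24 equally correlated at 0.3, 0.5 and 0.7: about 0.60, 0.46 and 0.31. This count is an upper bound only, because one model per scale may give one group-by-time test.

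**4. All scales must succeed.** Alpha holds. Taking d = 0.5 on every scale at an effective 52 per group and one-sided 5%, joint power for eight independent scales is 0.813⁸ = 0.19. Positive correlation raises it, but it cannot exceed the 0.81 of a single scale, which would need perfect correlation.

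**5. Alpha split over eight scales.** 0.05/8 = 0.00625. At an effective 52 per group, t-test power per scale is 0.51 one-sided and 0.41 two-sided. The like-for-like falls are 0.81 to 0.51 and 0.71 to 0.41.

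**6. One instrument and one contrast designated.** No multiplicity arises, and the one-test calculation applies as it stands.

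**The case against.** The strongest objection is that the article states no any-scale rule. Alpha is inflated only under such a rule, and a designated scale, a composite or a multiplicity procedure might stand in an analysis plan that is not shown. The first half is right, so a reader who infers that the trial's false-positive rate is several times 5% goes further than the text. The second half does not remove the point. What the primary outcome is belongs to the protocol, and the article states it as eight instruments beside a one-test sample size.

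Four further inferences are tempting and not supported:

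- **That resilience is primary in one place and secondary in another.** Both the abstract and Measurements make resilience *factors* and associated measures secondary (SOP-2, IE-4, ASKU-3, OSSS-3). Resilience itself (BRS) is primary. The two places agree.
- **That 24 tests will be run.** The planned multilevel model may cover all waves in one test per scale, so eight is the safer count.
- **That power falls from 0.80 to about 0.4 because of multiplicity.** Part of that fall is the change from a one-sided to a two-sided test. For the same reason, a required number per group for split alpha should not be taken from a two-sided test and set against recruitment, least of all without the clustering factor of 1.404.
- **That stressor exposure cannot be an outcome at all.** FGP support also addresses bureaucratic, economic and social needs, so some exposure could respond to it. This is a reason to keep it as a secondary outcome. It does not make it evidence of quality of life.

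**Conclusion.** The point holds. The primary outcome is not reduced to one variable or one decision rule, and the stated alpha and power cannot both apply to the list as it stands. Under an any-scale rule, alpha fails: 19% to 34% in either direction and 10% to 18% in the favourable direction, for correlations from 0.7 down to 0. Under an all-scales rule, alpha holds and power drops below the planned 0.80. Under an even split of alpha, power per scale is about 0.51 one-sided or 0.41 two-sided. A defined composite or one designated scale would preserve both figures, but the article gives neither.

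These sizes rest on eight scores (one per instrument), on assumed equal correlations, on d = 0.5, and on 73 evaluable families per group being worth 52. The even split is conservative for correlated scales. The article does not show which rule the investigators intend, so the finding is that the rule is open; a particular error rate is not established. The change should be made before the follow-up data are compared, because the primary claim is otherwise undefined.

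**What to change.** Before any follow-up comparison is run:

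1. Designate one quality-of-life instrument as primary. The choice is the sponsor's; FaBel-20 or WHO-5 are examples, and nothing in the article ranks one above the other.
2. Designate one contrast, for example the group difference in change from t0 to t3, and state whether the test is one- or two-sided. If it is two-sided, the basis of 52 must be revisited, since a single two-sided test then has power 0.71.
3. Make the remaining scales on the primary list secondary, tested in a fixed order or with Holm's procedure, and report t1 and t2 as supportive.
4. Do not let MIMIS or LEC carry the primary claim. Their t0 values can serve as covariates.

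The cost is wording in the protocol and analysis plan and an update of both registry entries. No increase in sample size is needed for multiplicity. The downside is that the other scales can no longer carry a primary claim alone.

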### Hypotheses

The development and systematic establishment of the three FGP core processes of a) structured assessment of the needs and requirements of families, b) counseling and coordination function and c) opening up accesses to needs-based support and relief offers in the regional supply network greatly contrast with the regular supply:

better recognition of the needs and requirements of families with children in need of care, across service providers and payers, and thus being addressed in a targeted and timely manner;more relief for families with children in need of care, and family care system strengthened;improved health, care and quality of life for families and children in need of care.

In the quantitative research part of the project, a prospective design is used to examine whether and to what extent the FGP intervention, coordination and family support as well as network support is suitable for achieving the care goals. Hypotheses are that through the intervention:

Access to care for families with children in need of care is improved.Over-, under- and misuse of health services is avoided.The family is strengthened as the most important resource for quality of life.

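### Avoidance of over-, under- and misuse of services is stated as an effect hypothesis of the controlled quantitative part, but its only named source is interviews with the FGPs, which give no control comparison

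*Protocol article*

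**What the plan says.** Four places in the protocol article bear on this point.

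- **Hypotheses.** The list is introduced with "In the quantitative research part of the project, a prospective design is used to examine whether and to what extent the FGP intervention", followed by the aim of judging whether the care goals are reached. Three effects of the intervention follow: better access to care, "Over-, under- and misuse of health services is avoided", and a strengthened family.
- **Design.** The quantitative part is described as "A non-randomized controlled study (quantitative online survey) over 18 months is ongoing with four measurement points". On who receives what: "In contrast to the control group, which is supported by standard care, the intervention group receives an FGP".
- **Measurements.** The primary and secondary survey outcomes are listed first. The nearest survey item is "Knowledge and use of support services [33"], placed under access to care. After the list comes a separate statement: "To assess possible over-, under- and misuse of health services the results of the process evaluation will be used". The next sentence names method and informants: "For this purpose, all FGPs involved are questioned by means of guideline-based qualitative interviews".
- **Statistical analysis.** The longitudinal data go into multilevel regression models, with interaction effects for intervention versus control.

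**The concern.** A hypothesis that something is avoided through an intervention is a comparative, causal statement. It needs an observation of what happens without the intervention, and in this design the control group under standard care supplies that. Placed among the hypotheses of the quantitative part, the second hypothesis reads as one that the controlled comparison will answer.

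The source named for it cannot do so. The interviews hold information only about families who have an FGP, and it is given by the people who provide the service. They can show how FGPs recognise and deal with inappropriate use. They cannot show that such use is less frequent than under standard care.

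What is at stake is how the result is read. The Discussion says that the results will eventually be applied in standard care. If the final report says something favourable about over-, under- or misuse, a reader of the Hypotheses section would take it for a finding of the controlled study.

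**Working it through.** No calculation decides this point, and the article gives no figure for it that could be reproduced. The check follows hypothesis 2 through the article and asks at each step what it would need.

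1. **Type of claim (Hypotheses).** An effect of the intervention, assigned to the quantitative, prospective part. Needed: a variable for over-, under- or misuse, observed in both groups.
2. **Comparator (Design).** Standard care, in a control group of 102 families. Only the intervention group has FGPs.
3. **Variable (Measurements).** None of the listed primary or secondary survey outcomes is designated as a measure of over-, under- or misuse. The article assigns that assessment to the process evaluation.
4. **Informants (Measurements).** All FGPs, in qualitative interviews. Combined with step 2, control families with an FGP who could report on them: 0 of 102. This count applies to the interviews only.
5. **Analysis (Statistical analysis).** The group comparison is an interaction effect in the longitudinal data. From step 3, those data hold no variable designated for hypothesis 2, so the comparison has nothing to act on for it.
6. **Limitations (Discussion).** The impact analysis of FGPs is said to use only self-reported outcomes, and reports by others, such as clinical data, are not planned. This gives no sign of a further source on service use. What an FGP says about a family's use of services is also not the family's own report, so on the article's own account the interviews sit outside the impact analysis.

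Could the service-use item in the family survey fill the gap at step 3?

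| | Hypothesis 2 | Service-use item |
|---|---|---|
| Object | health services | support services |
| Assigned to | process evaluation | access to care (matches hypothesis 1) |
| What is judged | too much, too little or wrong use | knowledge and use, as named |
| Groups | FGP families only | both groups |

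The item has the missing control group but not the missing content. As named, it does not say whether use was appropriate. The article also expects FGP networks to open up regional offers that families did not know of, so higher use would be an expected sign of better access. A rise could not be read as over-use, nor its absence as avoided misuse. At most the item gives some information on under-use.

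**The case against.** The strongest reply is that the article is open about what it does. It speaks of assessing possible over-, under- and misuse, keeps this apart from the survey outcomes, assigns it to the process evaluation and announces no test. Qualitative process evaluation is a legitimate method, and a fuller protocol may describe further components of it. Control families are not silent about care either: the survey asks about satisfaction with care, its coordination, and knowledge and use of services.

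Much of this stands, and it rules out several stronger readings that a reader might infer:

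- **That the study has no control data bearing on service use.** It has some. The count of 0 of 102 holds for the interviews, not for the survey.
- **That the sponsor plans an effectiveness claim from the interviews.** The article does not say so. The risk comes from where the hypothesis is placed, not from an announced conclusion.
- **That the bias is known to favour the intervention.** This is plausible, since providers would be judging their own work, but the documents neither state nor quantify it.
- **That the service-use item could simply be named as the test of hypothesis 2.** It is already a planned outcome for access to care, and it does not measure over-use or misuse.

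What the reply does not remove is the conflict within the article. The Hypotheses section places the effect in the quantitative part, and Measurements fixes a source that cannot carry it. This is not detail left to an unseen document, because the article itself names method and informants. The limitations paragraph mentions self-report and limited numbers but not that one hypothesis lacks a comparator.

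**Conclusion.** The point holds as an inconsistency between a stated hypothesis and its named source. One of three effect hypotheses of the controlled part is to be assessed from interviews that have no control comparison, so the plan as written cannot show that over-, under- or misuse is avoided relative to standard care. It should be corrected. It does not threaten the trial: hypothesis 2 has neither a primary nor a secondary outcome designated for it, and the primary outcome, the sample size and the planned group comparisons stay as they are.

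The conclusion rests on two assumptions. The first is that the interviews named in the article are the only source for this hypothesis; a control-group source in a full protocol would change it. The second is that the service-use item measures what its name says; its content rests on a cited source that is not available here.

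**What to change.** 1. Remove hypothesis 2 from the hypotheses of the quantitative part.
2. Restate it as an exploratory, uncontrolled question of the process evaluation, for example how FGPs perceive and handle over-, under- and misuse in the families they support.
3. State under Measurements that the FGP interviews explain processes and cannot support a statement on effectiveness.
4. Optional: report the between-group change in the service-use item, from the multilevel model already planned, as limited supporting information on under-use only. Label it as not measuring over-use or misuse, and as assigned to this question after the study began.

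Adding a new measure of health service use in both groups is not a clean alternative at this stage. Baseline collection began in January 2022 and the 102 control families had consented by the end of September 2022, so families already surveyed would have no baseline value.

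The cost is a change of wording, with no new recruitment or data collection, and no additional model if the optional step is taken. The real price is that the study gives up a controlled claim on hypothesis 2.
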